### **Study Population & Recruitment Plan**

Study clinics: The study sites for this study are MUSC general medicine, endocrine, family medicine, and community primary care clinics. The investigative team has access to patients in these clinics and letters of support from key physician collaborators in each of these clinics are attached.

Recruitment Strategy: We will use two complementary approaches to identify eligible study subjects. The first method will consist of systematic identification of AA patients with T2DM. After obtaining IRB approval for a partial waiver of HIPAA, we will use clinic-billing records over the previous 12-month period to identify AA subjects with ICD-9 codes consistent with a diagnosis of T2DM. The physicians of eligible patients will be notified of their patients' potential eligibility and asked permission to enroll their patients in this study. The

second method will consist of referrals from physicians, other clinic staff such as nurses, or patients themselves in response to recruitment flyers for the study.

**Participant Payment:** Participants will receive \$25 each for completion of baseline and 3 month assessments for a total payment of \$50.

**Patient eligibility criteria:** The study inclusion and exclusion criteria are as follows

**Inclusion Criteria:** 1) Age  $\geq 21$  years; 2) Clinical diagnosis of T2DM and HbA1c  $\geq 8\%$  at the screening visit; 3) Self-identified as AA; 4) Subject must be taking an oral medication or insulin for diabetes to be able to assess medication adherence; 5) Subjects must be able to communicate in English; 6) Subjects must have access to a telephone (landline or cell phone) and/or ethernet for the study period; and 7) Subjects must be willing to use the FORA monitoring system for 3 months.

**Exclusion Criteria:** 1) Mental confusion on interview suggesting significant dementia; 2) Participation in other diabetes clinical trials; 3) Alcohol or drug abuse/dependency; 4) Active psychosis or acute mental disorder; and 5) Life expectancy  $< 12$  months.

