#### 2. **The Financial Incentives Component.**

**Structure of Incentives:** The reward system is structured as follows:

- Low Frequency Financial Incentive – Group 1: the low frequency incentive structure will receive a reward for absolute percentage drops in HbA1c from baseline at 3-month follow-up, up to \$300.
  - After 3 months, if their HbA1c has dropped 2% from baseline, or absolute HbA1c is 7%, they will receive a reward of \$300, for a 1% drop, or an absolute HbA1c between 7 and 8 they will receive a reward of \$150.
- Moderate Frequency Financial Incentive – Group 2: the moderate frequency incentive structure will receive a reward or uploading glucose measurements, and absolute percentage drops in HbA1c from baseline at 3-month follow-up, up to \$300.
  - Each week participants in Group B can receive up to \$10 for uploading glucose measurements and having good glucose control throughout the week. For each day they upload at least one glucose measurement, they will receive \$1 (up to \$7 at the end of the week). If they upload measurements every day of the week and their average glucose measurements at the end of the week are 150 or below they will receive an additional \$3. Up to \$10 per week for 3-months.
  - After 3 months, if their HbA1c has dropped 2% from baseline, or absolute HbA1c is 7%, they will receive a reward of \$170, for a 1% drop, or an absolute HbA1c between 7 and 8 they will receive a reward of \$85.
- High Frequency Financial Incentive – Group 3: the high frequency incentive structure will receive a reward or uploading glucose measurements, attending educational sessions, and absolute percentage drops in HbA1c from baseline at 3-month follow-up, up to \$300.
  - Each week participants in Group A can receive up to \$10 for uploading glucose measurements and having good glucose control throughout the week. For each day they upload at least one glucose measurement, they will receive \$1 (up to \$7 at the end of the week). If they upload measurements every day of the week and their average glucose measurements at the end of the week are 150 or below they will receive an additional \$3. Up to \$10 per week for 3-months.
  - Participants can also earn \$5 each week if they attend the educational session. Educational sessions will last for 8 weeks, so they can receive up to \$5 per week for 8 weeks.

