### **Potential Risks**

Potential risks to the patient include possible violation of the patient's privacy, discomfort with questions on the research questionnaire, discomfort and bleeding from blood draws, discomfort with BP measurement, and psychological distress. Details on how these risks will be minimized are discussed under adequacy of protection against risks below.

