### **Protection against Risk**

**A.** Patients will be protected against potential risks as follows:

**1. Psychological Distress:** Because we will be administering a questionnaire that measures the presence of depression, we will take several steps to ensure the safety of all research participants. RAs will be trained by the PI to identify patients who meet criteria for depression on the PHQ-9. Subjects' who screen positive for depression will be notified during the visit and verbally instructed to seek care from their primary health care provider (PCP). They will also be given the 24-hour MUSC crisis psychiatry telephone service and told to call if they experience acute worsening of symptoms before they can be seen by their PCP.

**2. Venipuncture (blood drawing):** To reduce the risks of discomfort and bruising, venipuncture will be performed by trained personnel. To reduce the risk of fainting, blood will be drawn while subjects are in a seated position. The amount of blood that will be drawn, approximately 10cc, is not considered to pose a health risk for most adults. .

**3. Blood Pressure Measurement:** To lessen any associated risks, blood pressure measurements will be performed only by trained personnel utilizing a standardized protocol. Subjects with elevated blood pressure will be advised to contact their primary care provider. Those with potentially life threatening blood pressure readings will be sent to a local emergency room for treatment.

**4. Administration of Research Questionnaires:** Some participants might be offended by detailed questions about emotional or physical health status and impairment, and healthcare utilization. All participants will be informed at the outset that they may terminate participation at any point. Our past research suggests that data

collection using these measures can be conducted without undue psychological distress or exacerbation of symptoms among study participants.

**5. Unknown risks:** Subject participation in research may have other unknown risks. The researchers will advise subjects if they learn of emerging information that might alter subjects' decisions to participate in this study.

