**B.** Subjects requiring medical or other professional intervention for study-related events will be provided with appropriate and timely medical guidance by the designated medical monitor ([name] – board certified internist). [name] will have oversight on medical risks and will review all adverse events and report them to the IRB in accordance with the MUSC IRB Adverse Event Reporting Policy. The results of subjects' clinical assessments will be available within a few days of their study visit. [name] will review and advise subjects of these results by phone and, at their request; will also advise their personal physician of the results.

**C.** To protect against the potential risk of loss of confidentiality and/or breach of privacy, data will be compiled using codes in lieu of personal identifiers. Access to study data will be limited to research personnel. Development of and security oversight for the electronic database for this study will be performed by the study statistician. Paper documents pertaining to this study will be stored in locked file cabinets and electronic data will be entered into secure, password-protected databases developed for this study by the research assistants. The PI will perform periodic review of the data entry process to ensure accuracy of recording. When study results are published or presented, only aggregate reports of the results will be used and participants' identity will not be revealed. A file of name, contact address, telephone number, and other research identification numbers will be stored separately on paper and on computer, for purposes of audit by the sponsor (NIH) and MUSC IRB, if necessary.

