### **4. IMPORTANCE OF KNOWLEDGE TO BE GAINED**

The proposed study is innovative for a variety of reasons. First, behavioral economics is an emerging area of research that is not well tested in diabetes. Even though it is generally accepted that financial incentives can act as motivators to effect change in personal health behaviors (Sutherland 2008), few studies have assessed the effect of financial incentives on improving metabolic outcomes in T2DM. More importantly, there is little data on the effectiveness of financial incentives as motivators of behavior change in AAs. Second, the culturally-tailored education and skills training intervention proposed in this study is innovative because it targets patient level factors for which there is strong evidence of differences between AAs and Whites with T2DM (i.e. diabetes knowledge, self-management skills, empowerment, and fatalism/perceived control) (Egede 2005, Egede 2004, Nwasuruba 2007, Anderson 1995, Egede 2010). In addition, the intervention focuses on four key behaviors (physical activity, diet, medication adherence, and self-monitoring of blood glucose); maintains adequate dose and intensity of the intervention by delivering the intervention weekly for 12 weeks. Third, there are no large RCTs that have examined whether financial incentives augmented telephone-delivered diabetes education and skills training intervention will lead to greater improvements in metabolic control compared to usual care. Finally, the exploratory analyses will enable us to examine the effect of financial incentives augmented education and skills intervention on self-care behaviors and the mediation analysis will allow us to examine the contribution of self-care behaviors to improvements in metabolic control in African Americans with poorly controlled type 2 diabetes. With this approach, we can explore further targets for intervention in high risk African Americans with poorly controlled diabetes.

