### **5. DATA AND SAFETY MONITORING PLAN**

The data and safety monitoring plan will include an internal Data Safety Monitoring Committee (DSMC) and the institutional IRB. The purpose of the DSMC and IRB are to ensure the safety of participants and the validity and integrity of the data. Summaries of adverse events or patient safety concerns raised by the DSMC or IRB

will be made to NIH in the yearly progress unless the nature of a particular event is such that it bears reporting to NIH immediately.

DSMC: The internal DSMC will consist of the PI, biostatistician, co-investigators/consultants on the proposal, and a designated medical monitor ([name] – board certified internist who will have oversight on medical risks and review adverse events). The functions of the DSMC will include: 1) provide scientific oversight; 2) review all adverse effects or complications related to the study; 3) monitor accrual; 4) review summary reports relating to compliance with protocol requirements; and 5) provide advice on resource allocation. The DSMC will meet quarterly and as necessary by telephone. The recommendations of the DSMC will be reviewed and the PI will take appropriate corrective actions as needed.

Institutional IRB: The IRB will review and approve the funded protocol, review patient consent forms, ensure protection of patient privacy and safety, and monitor the study on an on going basis. Adverse events will be reported to the IRB as they occur. Annual reports to the IRB will indicate accrual rate, adverse events, new findings that may influence continuation of the study, and reports of the DSMC.

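### A low glucose reading can earn the weekly bonus in Groups 2 and 3, yet low blood glucose is missing from the risk list and no action is set for a low upload

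*Protocol*

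**What the plan says.** **Payment** (Protocol, The Financial Incentives Component). Every group has two HbA1c tiers at 3 months. The top tier is for a 2-point drop or an HbA1c of 7%; half of it is paid for a 1-point drop or a value between 7 and 8. Top payments are $300 in Group 1, $170 in Group 2 and $130 in Group 3. Groups 2 and 3 also earn $1 for each day with at least one upload. For a week with uploads on every day, if "their average glucose measurements at the end of the week are 150 or below they will receive an additional" $3. The bonus rule has an upper limit only.

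**Patients and intervention.** The inclusion criteria state "Subject must be taking an oral medication or insulin for diabetes", require a screening HbA1c of at least 8%, and require willingness to use the home monitoring system for 3 months. Importance of Knowledge to Be Gained says that the intervention works on physical activity, diet, medication adherence and self-monitoring together.

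**Risks and protections.** Potential Risks names privacy, questionnaire discomfort, "discomfort and bleeding from blood draws, discomfort with BP measurement, and psychological distress", and refers to the protections below it. Protection against Risk opens with "Patients will be protected against potential risks as follows" and numbers five items: distress, venipuncture, blood pressure measurement, questionnaires and unknown risks. For blood pressure it says "Those with potentially life threatening blood pressure readings will be sent to a local emergency room for treatment". A positive depression screen leads to referral to the primary care provider and a crisis line number. Glucose is in none of the five items.

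**The concern.** The trial pays patients to lower their glucose while they take drugs that lower it and are coached on diet, activity and adherence. Low blood glucose is the foreseeable harm of that combination, so it is not covered by an item on unknown risks. Staff must handle the uploads of Groups 2 and 3 to work out the weekly payment. Followed as written, the payment rule can release $3 because of a low reading, and no step tells anyone to respond to that reading.

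Patient safety is at stake first. What the pilot can say about harm is at stake second: no question about low glucose is scheduled, so an absence of reports would be weak evidence. Risk lists and clinical action limits are protocol content and are not normally left to a statistical analysis plan.

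**Working it through.** **1. Reproduce the stated maximum of $300.** Inputs are from The Financial Incentives Component.
- Group 1: 300.
- Group 2: 10 × weeks + 170. With 13 weeks, 130 + 170 = 300.
- Group 3: 10 × weeks + 5 × 8 + 130. With 13 weeks, 130 + 40 + 130 = 300.

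The figure reproduces with 13 paid weeks. With 12 weeks, Groups 2 and 3 reach only 290.

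**2. Part of the maximum that depends on glucose level** (HbA1c tier plus $3 bonus, 13 weeks).
- Group 1: 300 / 300 = 100%.
- Group 2: 170 + 13 × 3 = 209; 209 / 300 = 69.7%.
- Group 3: 130 + 13 × 3 = 169; 169 / 300 = 56.3%.

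**3. Can a low reading earn the bonus?** The protocol gives no unit for 150; mg/dL is assumed. Take one reading of 55 in a week with uploads every day.
- One reading a day, the other six at 165: (6 × 165 + 55) / 7 = 149.3, so the bonus is paid.
- Same week, low reading left out of the average but the day still counted: 990 / 6 = 165.0, so no bonus.

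In general, with n readings in the week and one of them equal to L, the bonus is paid when the others average at most (150 × n − L) / (n − 1). The low reading makes the difference when that average lies above 150 and up to this limit. For L = 55:

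| Readings per day | n | Limit for the other readings | Margin above 150 |
|---|---|---|---|
| 1 | 7 | (1,050 − 55) / 6 = 165.8 | 15.8 |
| 2 | 14 | (2,100 − 55) / 13 = 157.3 | 7.3 |
| 4 | 28 | (4,200 − 55) / 27 = 153.5 | 3.5 |

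The protocol asks for at least one reading a day, so one a day is the case with the largest effect.

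**4. Set the safety text side by side.**

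| Measure | When taken | Action stated |
|---|---|---|
| Blood pressure | Baseline and 3 months | Advice to contact the provider; emergency room if life threatening |
| Depression screen | With the questionnaires at study visits | Notification, referral, crisis line |
| Uploaded glucose | Up to daily, up to 13 × 7 = 91 days | None; used for payment and descriptive exploratory analysis |

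The measure taken most often, and the one that patients are paid to lower, is the one without an action.

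**The case against.** Much can be said for the protocol.

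- **Pay is capped.** A reader might infer that payment keeps rising as glucose falls. It does not. Nothing is added beyond the top HbA1c tier, and the bonus is a flat $3, so a weekly mean of 149 and one of 60 pay the same. The defect is the lack of an exclusion for low readings. This objection stands.
- **Oversight exists.** The medical monitor is to give timely medical guidance for study-related events and review all adverse events. Educators phone patients weekly for about 30 minutes. These are real safeguards, but adverse event review begins once an event is known, and no question on low glucose is specified for the calls. The monitor's review of results concerns visits: "clinical assessments will be available within a few days of their study visit". None of this is tied to readings uploaded between visits.
- **The committee need not wait.** A reader might infer that a low reading could sit for a quarter before anyone looked. The text does not support that: "The DSMC will meet quarterly and as necessary by telephone", and adverse events go to the ethics board as they occur. What is missing is anything that turns a low upload into a reported event.
- **Baseline risk is reduced.** Entry requires an HbA1c of at least 8%, no study change to diabetes drugs is described, and physicians are asked for permission to enrol patients found through billing records. This lowers the risk but does not remove it, since insulin users are eligible.
- **Other documents may help.** Consent pages and session content are not available and may tell patients how to treat a low value. That cannot be checked. The point concerns the protocol's own risk and protection sections, which are present.

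**Conclusion.** The point holds as a gap in the safety text joined to a payment rule that can work the wrong way. Low blood glucose is not a listed risk, a low upload has no stated response, and in Groups 2 and 3 such a reading counts toward a $3 bonus and can earn it. With one reading a day and one value of 55, this happens when the other six average above 150 and up to 165.8; at four a day the range ends at 153.5. These figures assume mg/dL and a single low reading in a fully uploaded week.

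A reader might want to turn this into an expected number of low readings or of patients affected. The documents give no rate for low readings and no within-patient correlation, so no such count is supported. Nor does the point touch the paired analysis of HbA1c change, which is unaffected. The change should be made for patient safety and for credible reporting of harm.

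**What to change.** **Potential Risks.** Add low blood glucose.

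**Protection against Risk.** Add a sixth item, for example: *The diabetes educator reviews uploaded readings in every group that uploads, at least when the weekly payment is processed and before each weekly call, and asks about low glucose at each call. A reading below 70 mg/dL leads to a call to the patient. A reading below 54 mg/dL is passed the same day to the medical monitor and the patient's physician. Patients are told that uploads are not watched in real time and how to treat a low value.* The limits 70 and 54 are proposals; the protocol gives none. Continue the review and the question through all paid weeks. The description of the education component gives 12 weekly sessions and the incentive section gives 8, so 13 − 12 = 1 or 13 − 8 = 5 paid weeks would otherwise have no call. Settle which is meant.

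**Financial Incentives Component, Groups 2 and 3.** Leave readings below the lower action limit (70 in the example) out of the weekly average for the bonus, with the day still counted as uploaded. A low value then cannot earn the bonus. This does not guarantee that lows are uploaded: a patient with another reading that day loses no money by leaving the low one out, which is why the weekly question is also needed.

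**Data and Safety Monitoring Plan.** Report low-glucose events by group to the committee.

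**Cost.** Four short text changes, with no new visits or patients. Payment already requires handling 40 × 13 = 520 patient-weeks of uploads in Groups 2 and 3; Group 1 adds up to 20 × 13 = 260 if it uploads. Covering the weeks without sessions needs 60 × 1 = 60 to 60 × 5 = 300 brief contacts. Calls triggered by readings come on top and cannot be counted from the documents. Two half-time educators must absorb this. Groups that upload more may also receive more contact, so report the number of calls by group.

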## **ADEQUACY OF PROTECTION AGAINST RISKS**

### **a. Recruitment and Informed Consent**

We will use two complementary approaches to identify eligible study subjects. The first method will consist of systematic identification of AA patients with T2DM. After obtaining IRB approval for a partial waiver of HIPAA, we will use clinic-billing records over the previous 12-month period to identify AA subjects with ICD-9 codes consistent with a diagnosis of type 2 diabetes. The physicians of eligible patients will be notified of their patients' potential eligibility and asked permission to enroll their patients in this study. After consent is obtained from the physicians, letters of invitation on clinic letterhead signed by the patient's physician will be mailed to patients from the study clinics. The letter will provide information about the study, explain the study requirements, and clarify that only subjects that meet certain criteria will be eligible to participate in the study. The letter will include an addressed and stamped post-card that subjects can mail back to indicate interest or lack of interest in participating in the study. In addition, the letter will provide a telephone number that interested subjects can call to receive detailed information about the study. In the letter, subjects will also be informed that they will receive a follow-up call in two weeks unless they mail back the post card or call to decline being contacted. Subjects that mail back the post card and express interest or call the provided telephone number will receive detailed information about the study. Subjects who agree to participate will be asked to provide written consent and will be scheduled for the initial screening assessment. The second method will consist of referrals from physicians, other clinic staff such as nurses, or patients themselves in response to recruitment flyers for the study. The PI will share the goals of the study and inclusion/exclusion criteria with physicians and clinic staff during clinic administrative meetings. Physicians and clinic staff will be asked to refer appropriate subjects to the study research assistants. In addition, IRB approved recruitment flyers will be posted in prominent locations in the study clinics.

